### Intervention

The mesh placement will be preceded by the plane preparation. The subcutaneous tissue will be dissociated from the anterior rectum-muscles fascia to allow the positioning of the transfix stitches necessary to the mesh fixation. Successively, the retro-muscular rectum muscles plane will be prepared by the separation of the rectum muscles from the posterior rectum-muscles fascia, preparing a 5–6-cm pouch necessary to the prosthesis positioning. The mesh will be fixed with at least 8 long-lasting absorbable transfix stitched (i.e., PDS 0) placed at the cardinal and inter-cardinal points. The prosthesis will be placed with at least a 5-cm overlap. If the peritoneal plane can be sutured, a Jackson-Pratt 10 suction drain will be placed under the prosthesis. A Jackson-Pratt 10 suction drain will always be placed over the prosthesis. Anterior rectum fascia will be closed by semi-continuous monofilament suture with an intermediate-reabsorbable-time suture. Another Jackson-Pratt 10 suction drain will be placed over the anterior fascia if the subcutaneous tissue is thick. No subcutaneous suture will be performed. Skin stapler or interrupted stitches will be used to close the skin plane.

The swine dermal collagen prosthesis that is used is manufactured by MECCELLIS BIOTECH ([name]) and is approved for use in Europe through a CE mark and is commercially available in Italy. The composition of the product is according to the product IFU. The swine dermal collagen prosthesis should be stored at room temperature in a dry environment.

Patients will be treated according to local hospital procedure. No additional costs (materials, salaries, other) due to the study will be charged to the hospital. Euroclone S.p.A. will supply all the prosthesis, as already happening for the usual clinical practice in the hospital the study is conducted in.

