### Patients recruitment

Enrolled patients scheduled to undergo urgent/emergent laparotomy in contaminated/infected fields with peritonitis, after signing the informed consent, and before the scheduled laparotomy will be randomized (Fig. 2) to be undergone to abdominal wall closure either with mass closure technique with simple running monofilament using a long-lasting absorbable suture material or with the same technique associated to the previous retro-muscular positioning of a swine dermal collagen prosthesis (sec. Rives-Stoppa technique). The patient is identified by the surgeon that visits him/her at the arrival in ED. If the patient is eligible the same surgeon acquires consent and gives all the information about the study and the type of mesh that is used for the study. There are no ethical concerns with the randomization, because the control group will receive the standard of care treatment while the study group will receive the same treatment plus the implantation of the biological prosthesis: this prosthesis does not have reported serious side effects and it is expected to reduce the abdominal wall complication rate. If the patient allows for the study but the randomization place him in the control group, he will be treated with the standard of care (suture with running monofilament using a long-lasting absorbable suture material).

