### Statistical analysis

Only the data of participants who complete the follow-up will be considered. Descriptive analysis will be performed for all pre-operative, operative, and follow-up information. For categorical variables, we will use chi-square test, for non-categorical one the *t*-test. The primary endpoint, % of patients presenting incisional hernia at 3, 6, and 12 months, will be analyzed between treatment groups using a logistic regression model, presenting odds ratio comparisons of the two. Surgery time, time to drain removal and length of stay in hospital will be analyzed between treatment groups using Student’s *T* test if data are normally distributed and with Mann-Whitney test if data are not normally distributed. The distribution of data will be evaluated with the Shapiro-Francia test. The number of patients who died will be analyzed between treatment groups using a chi-square test.

All statistical comparisons will be based on two sided tests with a 5% significance level.

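### The protocol gives two incompatible fascial closures for the mesh arm; if the Intervention section is followed, a hernia difference cannot be credited to the prosthesis alone

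*Protocol article*

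**What the plan says.** The Patients recruitment section of the protocol article defines both arms. Control closure is "mass closure technique with simple running monofilament using a long-lasting absorbable suture material". The mesh arm is closed "with the same technique associated to the previous retro-muscular positioning of a swine dermal collagen prosthesis". The ethical justification in the same section repeats the contrast: "the study group will receive the same treatment plus the implantation of the biological prosthesis".

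The Intervention section then gives the operative steps for the mesh arm. There the fascial instruction is: "Anterior rectum fascia will be closed by semi-continuous monofilament suture with an intermediate-reabsorbable-time suture". Long-lasting material is named in that section only for the stitches that fix the mesh.

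The Objective section attributes the hoped-for fall in hernia rate, from 50% to 20%, to the prosthesis.

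On drains, the Intervention section says: "A Jackson-Pratt 10 suction drain will always be placed over the prosthesis". Two further drains are conditional, one on whether the peritoneal plane can be sutured and one on subcutaneous thickness. No wall-drain rule is stated for controls. Time to drain removal is a secondary endpoint (Study endpoint section), and the Statistical analysis section says: "Surgery time, time to drain removal and length of stay in hospital will be analyzed between treatment groups".

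**The concern.** The primary endpoint is a hernia at the incision being closed, so the way the fascia is sutured bears on the outcome itself. The Background and rationale section lists surgical technique among the factors that affect wound healing. If suture class and stitch change together with the mesh, they are assigned with it, and randomisation cannot separate their effects.

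What is at stake is the meaning of the result. A positive trial would be read as evidence for the prosthesis, and a negative one as evidence against it, when either could partly reflect the closure. The justification for randomising also rests on controls receiving the same treatment without the implant.

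A smaller issue concerns time to drain removal: having a wall drain is a rule in one arm and is left unspecified in the other.

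**Working it through.** **Step 1: the two descriptions side by side.**

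| Element | Patients recruitment (both arms) | Intervention (mesh operation) |
|---|---|---|
| Suture class | long-lasting absorbable | intermediate absorption time |
| Stitch | simple running | semi-continuous |
| Layer | mass closure | anterior fascia named separately |
| Use of long-lasting material | the closure itself | mesh-fixing stitches only |
| Wall drains | not mentioned | 1 always, 2 conditional (minimum 1, maximum 3) |

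The first two rows cannot both hold for the mesh arm. Reading the Intervention sentence as applying to both arms does not help, because it would then contradict the stated control closure too. The Intervention section distinguishes long-lasting from intermediate material within one paragraph, so the difference is hard to dismiss as loose wording.

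**Step 2: what the comparison estimates.** Let C be hernia risk under control closure, M1 the risk with the mesh and the same closure, and M2 the risk with the mesh and the Intervention-section closure. Then

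C − M2 = (C − M1) + (M1 − M2).

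The first term is the mesh effect claimed in the Objective section. The second is the closure effect. If the Intervention section is followed, M1 is never observed and only the sum can be estimated. If the Patients recruitment section is followed, the mesh arm has risk M1 and the suture problem disappears.

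**Step 3: the plan's own figure.** Inputs: 50% versus 20% (Objective), two-sided 5% (Statistical analysis), 45 per arm (Sample size). Power is not stated; 80% is assumed. With p̄ = 0.35:

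n = [1.96·√(2·0.35·0.65) + 0.842·√(0.25 + 0.16)]² / 0.30² ≈ 38.5, so 39 per arm.

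With continuity correction: (38.5/4)·[1 + √(1 + 4/(38.5·0.30))]² ≈ 44.9, so 45 per arm and 90 in total. The stated size reproduces and is not in dispute.

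**Step 4: illustration of scale.** The documents give no closure effect, so the shifts below are assumptions. Uncorrected normal approximation with n = 45 per arm:

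power = Φ{[√n·(p₁ − p₂) − 1.96·√(2p̄(1 − p̄))] / √[p₁(1 − p₁) + p₂(1 − p₂)]}.

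For 50% versus 20%: (2.012 − 1.322)/0.640 = 1.078, giving 86%.

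| Assumed closure shift | Mesh inert, closure lowers risk from 50%: chance of a significant result favouring the mesh arm | Mesh works as planned, closure raises risk above 20%: power |
|---|---|---|
| 0 points | 2.5% | 86% |
| 5 points | 7% | 69% |
| 10 points | 16% | 49% |
| 15 points | 30% | 30% |

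**Step 5: drains.** With 45 planned per arm, every mesh patient who receives the procedure has at least one wall drain. The number of controls with a comparable drain is not stated and could lie anywhere from 0 to 45. A patient without a drain has no removal time, so the two sets compared need not be the randomised groups. The endpoint does not say which drain counts.

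**The case against.** The strongest reply is that the trial compares strategies. Randomisation makes closure with the prosthesis procedure versus standard closure a valid comparison whatever suture is used. That stands: what is lost is isolation of the prosthesis, not a valid treatment effect.

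Part of the difference may also belong to the operation. The Patients recruitment section announces a retro-muscular placement, so separate closure of the anterior fascia and a drain over the implant may come with it. That stands too, and it narrows the avoidable discrepancy to suture class and stitch. It does not make those the same in both arms, as the protocol says they are.

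Three stronger readings are tempting, and the documents do not support them.

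- A reader might infer that the effect cannot be attributed to the mesh at all. This holds only if the Intervention section is what surgeons follow, and only for the mesh in isolation.
- A reader might infer that several wall drains are compulsory in the mesh arm. Only one is; the other two are conditional.
- A reader might infer that the result on drain time is fixed by design. No removal time or rule is set in either arm, and Table 1 records drain placement and removal without restriction by arm, so controls may well have drains. The rule settles who has a drain, not how long it stays.

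Which drain counts, and how patients without one are handled, may be defined in the full protocol or analysis plan. Dropping the test would be a preference, since drain burden is a legitimate consequence of the mesh strategy.

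**Conclusion.** The contradiction on suture class and stitch is certain from the text and bears on the primary endpoint. The consequence is conditional: if the Intervention section is followed, every mesh-arm patient receives a different closure, and the trial estimates the effect of a package. That does not match the mesh-only contrast in the Patients recruitment section or the objective as worded.

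The size and direction of any closure effect are unknown. The figures of 7% to 30%, and 69% down to 30%, rest on assumed shifts of 5 to 15 points and show only that a moderate effect would matter at 45 per arm. This needs correction before further enrolment, because no analysis can separate the two components afterwards.

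The drain point is secondary. The placement rule is asymmetric for one secondary endpoint, the comparison is structurally unbalanced, and the primary endpoint is not touched.

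**What to change.** Reconcile the Patients recruitment and Intervention sections in one of two ways.

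1. State suture class and stitch technique consistently for both arms, marking any layer or drain that is inherent in the retro-muscular procedure. Which closure is used is the investigators' decision.
2. Withdraw the statements that the mesh arm has the control closure with only the implant added, and word the objective, comparison and conclusion as one closure package against the other.

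In either case, record which closure the patients already enrolled received.

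For time to drain removal, either interpret the result openly as a comparison between arms with different placement rules, or limit it to drains placed under a comparable rule in both arms.

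The cost is a protocol clarification and a check of operative reports for six patients (6/90, about 7% of the target). No extra patients or visits are needed.

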### Visit procedures

The randomization and the study data are collected using an online form (https://prophybiom.easycrf.cloud). The access at this form is allowed only at the participant at the study that has a username and password. Investigators who conduct follow-up assessments will not be blinded.

The study comprises of the following visits (Table 1):

**Table 1 Tab1:** Time and event chart

Nomenclature	Visit 1	Visit 2	Visit 3	Visits 4, 5, and 6
	Screening	Treatment	Discharge	Follow-up
	Screening, baseline	Surgery	Discharge	Follow-up
**Informed consent**	**√**			
**Inclusion/exclusion criteria**	**√**			
**Demographic data (sex, age, weight, height, BMI)**	**√**			
**Medical history/concomitant illness**	**√**			
**Physical examination**	**√**		**√**	**√**
**ASA classification**	**√**			
**Vital signs**	**√**	**√**		
**Body weight and height**	**√**			
**ECG (12 lead)**	**√**			
**Hematology and coagulation parameters**	**√**		**√**	
**Blood chemistry**	**√**		**√**	
**Antibiotic therapy**	**√**			
**Start of LMW heparin**	**√**			
**Concomitant medication**^**a**^	**√ continuously**			
**Start and end of surgery**		**√**		
**Site and length of incision**		**√**		
**Peritonitis grade assessment**		**√**		
**Peritoneal fluid sampling for microbiological examination**		**√**		
**Contamination assessment**		**√**		
**Intestinal resection**		**√**		
**Stoma creation**		**√**		
**Surgical complications**		**√**		
**Surgical drain placement**		**√**		
**Surgery report**		**√**		
**Time of drain removal**			**√**	
**Length of stay in hospital**			**√**	
**Post-surgical complications**			**√**	**√**
**Abdominal wall ultrasound**				**√**
**Adverse events**	**√ continuously**			

^a^This includes use of any blood transfusions that should be inserted in the CRF as type (red blood cells. FFP, platelets)

• Visit 1: Screening and baseline visit: screening of patient, baseline examination, pre-surgery assessment, informed consent

• Visit 2: Treatment visit: surgery

• Visit 3: Discharge from hospital: recording of post-surgical complications

• Visits 4, 5, and 6: Post surgery follow-up visits: at 3, 6, and 12 months post-surgery. All patients will perform an abdominal wall ultrasound to document the presence or not of incisional hernia. At the last visit, the data collected is the same of the other visits. The patients are called 15 days prior to the follow-up visit to remind them of the appointment.

In case of any premature discontinuation of the trial, the patient will, if possible, be called in for a last visit. Even if the patient is not able to attend, the End of Trial Form must be completed.

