#### Informed consent

All the criteria must be satisfied for included the patient in the study.

The exclusion criteria are:
Patients aged < 18 years oldInformed consent refusalNo clinical and/or laboratory and/or radiological evidence/signs of peritonitis of any originSurgical indication for laparotomies other than midline onePregnancy

The presence of even one of these exclusion criteria does not allow the patient to participate at the study.

The subject may withdraw at will at any time. The patient may be withdrawn from the trial at the discretion of the investigator for safety concerns. If the patient withdraws or is withdrawn at any time after receiving trial product, final safety information will be obtained. Patients who are deemed during surgery not suitable included in this protocol will be withdrawn from the study. In case a subject is being prematurely withdrawn from the trial, the investigator will ensure that the procedures for the last visit are undertaken, if possible. The primary reason (adverse event, non- compliance with protocol or other) for discontinuation must be specified in the CRF. A patient withdrawn from the study will be analyzed according to evaluability of subjects for analysis.

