### Assessments for efficacy

At discharge (visit 3), and at follow-up evaluations (visits 4, 5, and 6), the patient will be evaluated for post-surgical complications (such as hematoma/seroma, wound infection, reinterventions). Complications will be evaluated by the surgeon during surgery and at discharge. Any complications will be recorded in the CRF. If the complication leads to additional surgical interventions, it needs to be noted in the CRF. The need for blood transfusions will be noted in the CRF.

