### Follow-up of adverse events

During and following a subject’s participation in a clinical trial, the investigator/institution should ensure that adequate medical care is provided to the subject for any adverse events, including clinically significant laboratory values related to the trial. The investigator/institution should inform the subject when medical care is needed for adverse event(s) of which the investigator becomes aware. The follow-up information should only include new (updated and/or additional) information that reflects the situation at the time of the investigator’s signature. All non-serious AEs classified as severe or possibly/probably related to the trial product must be followed until the subject has recovered and all queries have been resolved. However, cases of chronic conditions can be closed with an outcome of “recovering” or “not recovered.” If subjects die from another event, these cases can be closed with an outcome of “recovering” or “not recovered.” The investigator must ensure that the worst case severity and seriousness is kept consistent through the series of adverse event form and related adverse event follow-up form(s). The investigator must forward follow-up information on non-serious AEs on the adverse event follow-up form. All serious AEs must be followed until the outcome of the event is recovered, recovered with sequelae, or fatal and until all queries have been resolved. For cases of chronic conditions and cancer or if the subject dies from another event, follow-up until the outcome categories are “recovered,” “recovered with sequelae,” or “fatal” is not required, as these cases can be closed with an outcome of “recovering” or “not recovered.” There are some adverse events that are expected for the population of the study like allergic reaction to the mesh, infection of the mesh, and migration of the mesh.

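### For a patient who stops early or cannot attend, no outcome collection to month 12 is stated, and the completers-only analysis then drops that patient

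*Protocol article*

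**What the plan says.** All references are to the protocol article.

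- **Visit procedures, on early stopping:** "In case of any premature discontinuation of the trial, the patient will, if possible, be called in for a last visit". If that fails: "Even if the patient is not able to attend, the End of Trial Form must be completed". The content of the form is not described.
- **Informed consent (withdrawal text):** when a subject is withdrawn early, "the investigator will ensure that the procedures for the last visit are undertaken, if possible". Also: "If the patient withdraws or is withdrawn at any time after receiving trial product, final safety information will be obtained". The primary reason must be given in the CRF, with adverse event, non-compliance and other as the examples. Withdrawn patients are to be analysed according to an evaluability rule that the article does not define.
- **Visit procedures, on the last visit:** "At the last visit, the data collected is the same of the other visits". It therefore includes the abdominal wall ultrasound.
- **Visit procedures, on contact:** "The patients are called 15 days prior to the follow-up visit to remind them of the appointment". No other purpose is given for this call.
- **Follow-up of adverse events:** "All serious AEs must be followed until the outcome of the event is recovered, recovered with sequelae, or fatal".
- **Assessments for efficacy:** complications are evaluated at discharge and at the three follow-up visits, and "If the complication leads to additional surgical interventions, it needs to be noted in the CRF".
- **Study endpoint:** the primary endpoint is the hernia rate at 3, 6 and 12 months. Mortality and morbidity are secondary.
- **Statistical analysis:** only participants who complete follow-up are considered. Deaths are compared by a chi-square test on their number.

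**The concern.** The last visit takes place when the patient stops, not at month 12. Someone who leaves at month 2 can have a complete last visit with ultrasound and still contribute nothing at 6 or 12 months. The article does not say that anyone then looks for a later death, re-operation or hernia repair, although these can be learned without a clinic visit.

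Early stopping is foreseeable here. Patients are randomised before laparotomy, those found unsuitable during surgery are withdrawn, and survivors of emergency peritonitis surgery may be too ill to return. If stopping is related to illness or to the abdominal wall, the patients left in the analysis are a selected group in each arm, and the selection may differ by arm. A comparison of numbers of deaths is especially exposed, because an undetected death cannot be counted and, read literally, a patient who dies before month 12 has not completed follow-up.

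**Working it through.** **1. The plan's own figure.** Inputs: 50% against 20% (Objective), two-sided 5% (Statistical analysis), 45 per arm (Sample size). Power is not stated; 80% is assumed.

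- Without continuity correction: n = [1.96·√(2·0.35·0.65) + 0.842·√(0.5·0.5 + 0.2·0.8)]² / 0.30² = (1.322 + 0.539)² / 0.09 ≈ 38.5, so 39 per arm.
- With correction: (38.5/4)·[1 + √(1 + 4/(38.5·0.30))]² ≈ 44.9, so 45 per arm and 90 in total.

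The 90 is reproduced. On this reading it holds no allowance for loss. If 10%, 20% or 30% do not complete, continuity-corrected power falls from 80.1% to 74.9%, 68.7% or 61.3%.

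**2. Do the stated provisions reach month 12 after stopping?**

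| Provision | What it captures | New events after stopping, to month 12? |
|---|---|---|
| Last visit, if possible | Examination, complications and ultrasound at stopping | No |
| End of Trial Form | Content not shown | Not stated |
| Final safety information | Safety data at withdrawal, after trial product | No |
| SAE follow-up | Outcome of events already known | No |
| Re-intervention in the CRF | Complications assessed at discharge and visits | Only if the patient attends |
| Pre-visit call | Reminder of an appointment | Not used for outcomes |

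The final safety information is tied to having received trial product. Read literally, that means mesh patients only, so ascertainment at withdrawal could differ by arm.

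**3. How far could missing outcomes move the hernia difference?** The article gives no dropout rate, so the losses are assumptions, taken as equal in both arms.

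With 7 of 45 missing per arm (15.6%), and 19/38 = 50.0% and 8/38 = 21.1% in attenders:

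- Control: from 19/45 = 42.2% (no missing patient has a hernia) to 26/45 = 57.8% (all do).
- Mesh: from 8/45 = 17.8% to 15/45 = 33.3%.
- Smallest difference: 42.2 − 33.3 = 8.9 points. Largest: 57.8 − 17.8 = 40.0 points.

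In general, with a fraction d missing per arm and 50% against 20% in completers, the limits are (1 − d)·30 ± 100·d points:

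| Missing per arm | Lower limit | Upper limit |
|---|---|---|
| 10% | 27 − 10 = 17 | 27 + 10 = 37 |
| 20% | 24 − 20 = 4 | 24 + 20 = 44 |
| 30% | 21 − 30 = −9 | 21 + 30 = 51 |

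These are logical extremes, not forecasts, and they leave out sampling error. In the 7/45 case, each missing outcome that is firmly established takes 1/45 = 2.2 points off the 31.1-point width.

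**4. Mortality.** The article gives no expected death rate, so no size is computed.

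**The case against.** A reader might infer that the plan asks for nothing but a form, or that outcomes after stopping are simply lost. The text supports neither. A last visit with ultrasound comes first where possible, final safety information is obtained, the time and event chart has adverse events recorded continuously, and known serious events are followed to outcome. The form's content is not shown, so it may already hold vital status. A reader might also infer that death, loss and refusal are merged in the CRF because only three reasons are named; that list is a parenthesis and does not show it. And it is an inference that the pre-visit call is made by telephone, or that it reaches patients who have stopped: it precedes a scheduled visit, which such a patient no longer has.

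The article condenses a fuller protocol, and details of forms and tracing are commonly left to it. That is fair as to form fields. But the article does set out the rule for early stopping, and that rule ends at the time of stopping. It also fixes the completers-only analysis outright.

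Two further objections stand. Quoting only the 9-point limit would be one-sided, since the same inputs allow 40 points. And remote contact can document a hernia but cannot exclude one as ultrasound can, so it narrows the main hernia analysis less than it improves survival, re-operation and repair data.

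**Conclusion.** The concern holds in this form: the article states no collection of survival, re-operation or hernia outcomes between early stopping and month 12, and the completers-only rule would set aside such patients even if their outcomes were known. This is a weakness that is cheap to correct. It does not show that the trial's result will be wrong, or in which direction it would move.

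The size depends on loss that the article does not state. With 7/45 missing per arm, the hernia difference is determined only to within about 9 to 40 points; with 10% to 30% loss, to within 17 to 37 up to −9 to 51 points. These ranges assume equal loss in both arms and attender rates close to the planned ones. That stopping is related to illness or wall problems is a judgement about this population, not a figure from the document.

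**What to change.** 1. **Collection (Informed consent, Visit procedures).** At each pre-visit call, and at 12 months for anyone who stopped visits without refusing further contact, record vital status and date of death, any abdominal re-operation or hernia repair with its date, and any diagnosed hernia. Use the patient contact and the centre's own records, and do so identically in both arms, whether or not a mesh was placed.
2. **Reasons.** Give death, loss to follow-up and withdrawal of consent their own discontinuation categories.
3. **Endpoint rules.** Count deaths in the mortality endpoint only, so that the primary endpoint does not become a composite. Count documented hernia repairs or diagnoses as hernia events. Keep patient-reported hernia without examination to a sensitivity analysis. State in advance how patients with no documented hernia and no ultrasound are handled.
4. **Analysis (Statistical analysis).** Replace the completers-only rule with analysis of all randomised patients with data, and reconcile it with the undefined evaluability rule in the withdrawal text. Without this step the recovered outcomes would be discarded; without steps 1 and 2 there would be little to analyse.

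Cost: a few CRF fields, a few minutes per call, an added month-12 contact and records check for patients who have stopped, and hernia reports that are less reliable than ultrasound.
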